### Outcome measures

The study has two primary outcomes: post-intervention tobacco-related knowledge and post-intervention skills for tobacco cessation assessed using a multiple-choice-based evaluation instrument and an OSCE, respectively. The secondary study outcomes are post-intervention attitudes towards tobacco cessation and self-efficacy in tobacco-cessation interventions assessed using a survey instrument. An additional secondary study outcome is the post-intervention performance difference in relation to tobacco-cessation skills in the practice setting assessed using the simulated client approach.

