#### Assessment implementation

The assessment instruments will be distributed to participants in both groups prior to, and following, the program. The assessment will be likely online using a survey software. Participants will be allowed a certain predetermined time to complete the evaluations. Unique participants’ codes will be created to link the pre to post data for the same participant.

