### Statistical analysis

Data will be analyzed using IBM SPSS (IBM SPSS® for Windows, Version 24.0; IBM Corp, Armonk, NY, USA). The Consolidated Standards of Reporting Trials (CONSORT) guidelines will be followed when analyzing the study data [34]. Demographic and other pharmacist education and practice-related questions, along with baseline knowledge, attitudes, and perceived self-efficacy, will be summarized using means and standard deviations for numeric variables such as age and year of experience and frequency distribution for categorical variables such as gender, country of education, etc. Those will be compared between the study groups so that differences will be used to adjust the primary analyses.

The primary analyses will include comparing post-knowledge scores between the two study arms using the independent *t* test and the skills-related scores on the OSCE using the same method. The secondary analyses will include adjusting the main analyses to any imbalances in baseline variables that are observed between the study arms. This will be done using the linear regression method. Moreover, knowledge scores will be compared within each study group using the paired *t* test. For outcomes that are dichotomous or that will be dichotomized, such as the percentage of pharmacists with a specific attitude or self-perceived efficacy, then the chi-squared test will be used to compare such outcomes between study groups and the McNemar test will be used to compare responses within each study group over time. Performance on the simulated patient will be compared in a similar manner as the outcomes above depending on whether it is dichotomized or not. In addition, repeated-measures analysis (depending on the scale of measurement for each outcome) may be used to detect whether there is an intervention × time interaction so that difference between study groups is changing over time or not. The level of statistical significance will be set at 5%.

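### For dichotomised attitudes and self-efficacy, the committed between-arm test leaves out the linked baseline answers, which by commitment enter only within-arm tests; the cost is efficiency, not validity

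*Protocol article*

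**What the plan says.** The Outcome measures section defines these endpoints by post-program status: "The secondary study outcomes are post-intervention attitudes towards tobacco cessation and self-efficacy in tobacco-cessation interventions assessed using a survey instrument". Both arms complete the instruments before and after the program, and under Assessment implementation "Unique participants’ codes will be created to link the pre to post data for the same participant".

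The Statistical analysis section covers outcomes that are dichotomous or will be dichotomised, "such as the percentage of pharmacists with a specific attitude or self-perceived efficacy". For these it fixes two tests:

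- Between arms, "the chi-squared test will be used to compare such outcomes between study groups". This has no baseline term.
- Within arms, "the McNemar test will be used to compare responses within each study group over time". This has no control group.

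Knowledge also gets a within-arm test: "knowledge scores will be compared within each study group", by paired t.

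Baseline enters in three other places. Baseline values are compared between the groups. The main analyses (knowledge and OSCE scores) are adjusted by linear regression, but only for imbalances that are observed. A repeated-measures analysis is optional: it "may be used to detect whether there is an intervention × time interaction".

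**The concern.** The trial's hypothesis is that trained pharmacists do better than controls. Only a between-arm comparison tests that, and for these outcomes no committed between-arm analysis uses the person's own baseline answer, although the data will be in hand.

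Two things are at stake. The randomised comparison gives up whatever precision the baseline answer would add. And separate p-values in each arm invite the reading that the program worked because one arm changed significantly and the other did not. Both arms answer the instruments twice and participants are unblinded, so some improvement without any program effect is plausible in either arm.

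**Working it through.** **Inputs from the protocol.** 54 evaluable per arm; a 27.5-point difference; 80% power; 5% significance (taken as two-sided); 10% loss; 60 randomised per arm.

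**Assumptions (not in the protocol).** The pre/post association, shown over a range; the control proportion; any gain shared by both arms.

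**1. The plan's own figure.** With the conservative variance at p = 0.5:

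n = 2 × 0.25 × (1.960 + 0.842)² / 0.275² = 51.9, so 52 per arm. The Fleiss formula with continuity correction for 50% versus 77.5% gives 54. Then 54 / (1 − 0.10) = 60. The stated figure reproduces, without any baseline adjustment.

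**2. What baseline adds for a binary outcome.** I simulated 40,000 trials per setting: latent bivariate-normal baseline and post answers, dichotomised, 54 per arm, baseline 36.25% in both arms, post 36.25% (control) versus 63.75% (intervention), which is 27.5 points. Three tests were compared: the post-only chi-squared; Cochran-Mantel-Haenszel (CMH) stratified by the baseline answer; and a difference-in-change comparison, which is what an intervention × time test amounts to with two time points.

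| phi (pre/post) | chi-squared | CMH on baseline | difference in change |
|---|---|---|---|
| 0 | 81% | 81% | 55% |
| 0.19 | 81% | 83% | 63% |
| 0.33 | 81% | 86% | 71% |
| 0.49 | 81% | 90% | 81% |
| 0.58 | 81% | 93.5% | 88% |

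A closed-form check agrees. Adjustment multiplies the variance by about 1 − phi², so at phi = 0.5 the effective size is 54 / 0.75 = 72 per arm. The normal-approximation power then moves from 82.5% to 91.8%. At phi = 0.3 it is 54 / 0.91 = 59.3 per arm and 85.9%. Starting from a baseline of 30% or 50% changes the levels (chi-squared 82% or 86%) but not the pattern.

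The optional interaction test is no substitute: it falls below the plain chi-squared until phi reaches about 0.5.

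**3. What dichotomising costs, kept separate.** On the latent scale 27.5 points centred at 50% is 2 × 0.352 = 0.70 SD. An unadjusted t test on that score has noncentrality 0.70 × √(54/2) = 3.66, hence about 95% power against 81% for chi-squared. That gain uses no baseline at all. It is available only where a scale score exists.

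**4. Within-arm tests when the program does nothing.** Both arms start at 36.25% and rise equally; exact McNemar test in each arm. Entries are the share of trials significant in the intervention arm but not in the control arm:

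| Shared rise | latent r = 0.3 | 0.5 | 0.7 |
|---|---|---|---|
| 10 points | 13% | 15% | 17% |
| 15 points | 22% | 24% | 25% |
| 20 points | 25% | 23% | 19% |

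With a shared gain of 0.2 to 0.3 SD and a cut at 0.3 SD, the same event occurs in 10% to 21%. With no shared rise it is about 3%. Chi-squared and CMH between arms stay at 4% to 5% throughout. The paired t test behaves alike: for gains of 0.2 to 0.3 SD and r of 0.5 to 0.7 its power p in one arm runs from about 0.30 to 0.80, and p(1 − p) is 16% to 25%.

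**The case against.** The strongest reply is that nothing here is wrong. The chi-squared test matches the endpoint as defined, keeps its type I error, and is the test the sample size rests on. These are secondary outcomes, and covariates for secondary outcomes are often left to an analysis plan. All of that stands except the last step: the protocol names the tests, so what it names can be improved.

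Three stronger readings are tempting, and the document does not support them.

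- A reader might infer that the program will be judged by the McNemar tests. The hypothesis is stated between groups, the within-arm tests stand beside the between-arm test rather than in its place, and no conclusion is tied to them.
- A reader might infer that baseline is never used between arms. Baseline values are compared between groups and the interaction analysis is permitted; what is missing is a commitment.
- A reader might infer a very large power loss by setting the chi-squared on a cut score against covariance analysis on the full score. Most of that gap comes from dichotomising, as step 3 shows. Nor does the protocol say that every attitude or self-efficacy score will be dichotomised.

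It is also fair that removing the within-arm tests would be more than is needed, and that logistic regression reports a conditional odds ratio and can be unstable for near-ceiling items at 54 per arm. The stratified CMH test is an alternative for such items.

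**Conclusion.** The point holds as a free improvement on secondary outcomes. For dichotomous or dichotomised attitudes and self-efficacy, the committed randomised comparison ignores baseline answers that are collected and linked. At the planned 27.5-point difference this costs about 2 to 9 points of power for phi between 0.2 and 0.5, and nothing if the pre/post answers are uncorrelated. The correlation is an assumption. The stated 80% power is met and the sample size is unaffected.

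The within-arm tests carry an interpretation risk of roughly 10% to 25% for significance in the intervention arm only, conditional on an assumed equal improvement in both arms. It becomes an error only if someone draws an effectiveness claim from those p-values.

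**What to change.** In the Statistical analysis section:

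1. Make the committed between-arm analysis of each attitude and self-efficacy outcome a model with that outcome's own baseline as covariate: linear regression on the scale score where one exists; logistic regression, or CMH stratified by the baseline answer, for truly binary items. Apply it whether or not a baseline imbalance is seen.
2. Use this model in place of the optional intervention × time test for outcomes measured before and after the program.
3. Label the within-arm paired t and McNemar results descriptive, and state that no claim of effectiveness rests on them.

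The cost is analysis wording. The data collection is already planned, and linear and logistic regression run in the planned SPSS. No change to sample size or visits is needed.

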
### Sample size estimates

With 54 pharmacists per group, the study will have an 80% power to detect an effect size of 0.60 between the study groups for two primary outcomes which are numeric (knowledge and skills scales) using the independent *t* test with a significance level of 0.025%. In addition, with 54 pharmacists per group, the study will be able to detect a difference of at least 27.5% between the two study groups for any dichotomous outcome using the chi-square test with 80% power and a significance level of 5%. Assuming a loss-to-follow-up rate of 10%, the study will randomize 60 pharmacists per group for a total of 120 pharmacists. With over 1000 community pharmacists practicing in Qatar, including 60 pharmacists in each group is achievable. We will select a random sample of 200 pharmacists for recruitment as we anticipate that some pharmacists will not accept to participate. Once the sample size of 120 is reached the recruitment will stop.

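### The analysis section sets one 5% significance level, while the sample size for the two primary outcomes works only at 2.5% each and misprints that level as 0.025%

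*Protocol article*

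**What the plan says.** All places are in the Methods/design part of the protocol article.

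- Outcome measures: "The study has two primary outcomes: post-intervention tobacco-related knowledge and post-intervention skills for tobacco cessation". The abstract and the study objectives name the same two.
- Sample size estimates, primary outcomes: "With 54 pharmacists per group, the study will have an 80% power to detect an effect size of 0.60 between the study groups", for two numeric outcomes compared by independent t test, "with a significance level of 0.025", followed in print by a per cent sign.
- Sample size estimates, next sentence: a separate level is given "for any dichotomous outcome using the chi-square test with 80% power and a significance level of 5" per cent.
- Sample size estimates, dropout: "Assuming a loss-to-follow-up rate of 10%, the study will randomize 60 pharmacists per group for a total of 120 pharmacists".
- Statistical analysis, primary outcomes: "The primary analyses will include comparing post-knowledge scores between the two study arms using the independent" t test, with the OSCE scores handled in the same way. No level is attached to either test.
- Statistical analysis, last sentence, after the adjusted, within-group, dichotomous, simulated-client and repeated-measures analyses: "The level of statistical significance will be set at 5" per cent.

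**The concern.** The two sections give different levels for the same two tests. The sample size section sets the primary outcomes apart from the dichotomous outcomes with a stricter level. The analysis section has a single level and does not carry the stricter one over.

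The practical question is what happens to a primary p-value between 0.025 and 0.05. Under the level that produced the sample size it is not significant. Under the closing sentence of the analysis section, read literally, it is. A reader cannot tell which rule governs, and the choice could be made after the data are seen. If the literal rule is followed and either outcome can carry a positive claim, the error protection that the sample size was built on is lost.

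The printed 0.025% adds to the problem. It is one hundredth of the value that the calculation needs, so the one place that gives a level for the primary outcomes does not give a usable one.

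**Working it through.** **Inputs.** From Sample size estimates: standardised effect d = 0.60, power 80%, 54 per arm, equal allocation, dropout 10%. From Outcome measures: two primary outcomes. Assumed because not stated: two-sided tests (step 1 supports this) and the correlation between the two outcomes (range 0 to 0.9).

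**Step 1. Reproduce the 54 per arm and find which alpha produces it.**

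Normal approximation: n per arm = 2 (z₁₋α/₂ + z₀.₈₀)² / d², with z₀.₈₀ = 0.842 and d² = 0.36.

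- α = 0.025: 2 × (2.241 + 0.842)² / 0.36 = 52.8, so 53.
- α = 0.05: 2 × (1.960 + 0.842)² / 0.36 = 43.6, so 44.
- α = 0.00025 (the printed 0.025%): 2 × (3.662 + 0.842)² / 0.36 = 112.7, so 113.

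The noncentral t, which matches the planned test, gives slightly larger numbers:

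| Two-sided alpha | n per arm, normal | n per arm, noncentral t | Power with 54 per arm, noncentral t |
|---|---|---|---|
| 0.05 | 44 | 44.6 | 87.1% |
| 0.025 | 53 | 54.08 | 79.9% |
| 0.00025 | 113 | 116.05 | 26.0% |

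Only two-sided 0.025 matches the stated 54 and 80%. A one-sided 0.025 does not: it gives 44 per arm, the same as two-sided 0.05. The dropout step also agrees: 54 / (1 − 0.10) = 60 per arm, 120 in total.

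The design level is therefore 0.025 = 0.05 / 2 per primary outcome, and the printed 0.025% is evidently a slip for 0.025 or 2.5%.

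**Step 2. Error rate if both primary outcomes are tested at 5%.**

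This is the chance of at least one false-positive primary result when both null hypotheses are true.

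- Independent outcomes, 5% each: 1 − (1 − 0.05)² = 0.0975. Upper bound: 2 × 0.05 = 0.10.
- Independent outcomes, 2.5% each: 1 − (1 − 0.025)² = 0.0494. Upper bound: 2 × 0.025 = 0.05.
- Correlated outcomes: 1 − P(|Z₁| < c, |Z₂| < c) from the bivariate normal, with c = 1.960 for 5% and c = 2.241 for 2.5%.

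| Correlation | 5% per test | 2.5% per test |
|---|---|---|
| 0 | 9.75% | 4.94% |
| 0.3 | 9.5% | 4.8% |
| 0.5 | 9.1% | 4.6% |
| 0.7 | 8.3% | 4.3% |
| 0.8 | 7.8% | 4.0% |
| 0.9 | 7.0% | 3.6% |

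**Step 3. How often the two rules would disagree at the planned effect.** For one outcome with d = 0.60 and 54 per arm, the chance of a p-value between 0.025 and 0.05 is the difference in power: 87.1% − 79.9% = 7.2 percentage points.

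**The case against.** The best defence is that the closing 5% is the overall level and that the sample size section governs the two primary tests. The sentence on the primary t tests carries no level of its own, and the 5% line is a general statement at the end of the section. Read this way, the two sections agree once the misprint is corrected, and there is no inflation. This reading is possible, so it would go too far to say that the protocol expressly assigns 5% to each primary test. But the sentence does not call the level overall or familywise, and it follows a list of individual tests for which 5% can only be a per-test level. The ambiguity therefore stands.

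A second defence is that success might require both outcomes to be significant, in which case 5% each would inflate nothing. The article states no such rule. A condensed article may leave the rule to the full plan, so its absence is not held against it here. However, a both-must-succeed rule needs no division of alpha, and the reduced level behind the 54 per arm points the other way.

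A third is that the reach is small: only p-values between 0.025 and 0.05 are affected, and neither the sample size nor the data collection changes. That is correct. It limits the cost of the fix but does not remove the need for one rule fixed in advance.

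**Conclusion.** The point holds as a conflict between two stated levels. The sample size rests on two-sided 2.5% per primary outcome, and the analysis section gives 5% with no exception for those outcomes. The 2.5% is inferred from the arithmetic. The article prints 0.025% and nowhere says that alpha is divided.

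Read literally, the chance of at least one false-positive primary result is 7.0% to 9.75% over correlations from 0.9 down to 0, against at most 5% at the design level. These figures assume that 5% applies to each test, that either outcome alone can count as success, and that both null hypotheses are true.

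A reader might infer two stronger conclusions, and the document supports neither:

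- That the error rate is simply 9 to 10%. That holds only for correlations up to about 0.5, and no correlation is given.
- That the trial is badly underpowered because the printed 0.025% would need 113 or more per arm. The match of 54 per arm, 80% power and effect size 0.60 at alpha 0.025 shows a printing slip, not a shortage of participants.

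**What to change.** Make two changes together. If only one is made, the sections will still disagree.

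- In Statistical analysis, state that each of the two primary comparisons is tested two-sided at 2.5%, which keeps the overall level at 5%, and that the 5% level applies to secondary outcomes without adjustment for multiplicity. Holm's procedure is an acceptable option: the smaller primary p-value is tested at 2.5% and, if it is significant, the other at 5%. It also keeps 5% overall and never has less power than 2.5% for both.
- In Sample size estimates, correct the printed 0.025% to 2.5% (0.025) and say that the test is two-sided.

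The cost is a sentence or two. The 54 per arm and the 120 to be randomised stay as they are. The primary threshold is stricter than the literal 5%, but power at that threshold (79.9% with 54 per arm) is what the design already planned for.

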### Ethical considerations and data handling

The study protocol and all related instruments and forms were granted ethical approval by the Qatar University (QU) Institutional Review Board (IRB) (QU-IRB 906-E/18). All data related to the study will be kept confidential and will be retained in a password-protected database maintained along with all related study documentation in a locked cabinet at QU College of Pharmacy. Participation in the study will not cause any harm to participants and, as a result, no data monitoring committee will be assigned. Only the study team will have access to the final study dataset. Any protocol modifications will be communicated with QU IRB. The study results will be presented via poster or oral presentations in international conferences and will be published in peer-reviewed journals. The authors of the final study manuscript will have considerable contributions to the design, implementation, assessment, and reporting of the study.

### Monitoring

The study progress will be monitored closely by the study team. Meetings will be held to guide the study towards its aim and objectives with team involvement. A weekly meeting involving all the team members including RAs will be organized. The study team will be in direct touch with each other and RAs through electronic communication (Google® docs and emails). Electronic communication will help in keeping the minutes of the meetings, will provide easy access to any study-related document, and will facilitate online sharing of information. The study team will also conduct ad-hoc meetings at least biweekly to monitor data collection, to check protocol adherence, to review appropriate documentation and to address any issues that might arise.

## Discussion

Many published studies have demonstrated the impact of tobacco-cessation-related training on pharmacists’ knowledge, self-efficacy, confidence, and ability to provide tobacco-cessation counseling [35]. This study will be expected to be the first randomized controlled trial conducted within Qatar and the ME that includes designing, implementing, and evaluating an intensive education program on tobacco-cessation treatment for pharmacists in Qatar. The findings of this study should have far-reaching implications to add to the existing body of knowledge about the management of what is known to be an endemic health hazard costing countries billions of dollars every year and negatively affecting the quality of life of millions of people and their families. In response to the health effects of smoking and its spread, the WHO introduced strategies to combat smoking through the implementation of its Framework Convention on Tobacco Control (FCTC) entitled MPOWER. The six measures under this strategy include monitoring tobacco use and prevention policies; protecting people from tobacco use; offering help to quit tobacco use; warning about the dangers of tobacco; enforcing bans on tobacco advertising, promotion, and sponsorship; and raising taxes on tobacco [1]. Several measures under the “offering help to quit tobacco use” strategy require skilled and trained personnel. The role of pharmacists in helping patients quit smoking is well established. Pharmacists could use their skills and training to become providers of a credible source of health information [9]. However, the skills to help people change their unhealthy behaviors are not generic. The proposed program aims at providing specialist-level training for generalist pharmacists to provide them with the skills and knowledge tailored to assist people who smoke to quit smoking.

Tobacco cessation is one of the most cost-effective of all healthcare interventions and a successful program within the healthcare system will release resources for other needs. The FCTC contains specific obligations concerning tobacco dependence and cessation, including the establishment of programs for diagnosing, counseling, preventing, and treating tobacco dependence [36]. This study builds the foundation for a new form of collaborative interprofessional healthcare team to confront the endemic nature of smoking. The training team consists of expertise from academia and healthcare organizations in the three countries: Qatar, New Zealand, and Malaysia. The training program is anticipated to generate individual healthcare practitioners with the right set of skills and competence to join the current teams at the Tobacco Control Center-WHO Collaborating Center at Hamad Medical Corporation in its efforts within a unique professional approach. This study has the potential to create the right environment for a scheme of continued and seamless smoking cessation care in which referral of patients between primary care and Hamad Medical Corporation (HMC: the main public hospital in Qatar) can be facilitated. The experience and information generated by this study in these aspects should be of interest at the national, regional, and international level.

